#### Monitoring phase

At the clinic, participants will be provided with a PAM and instructed to keep the monitor at home and take it out with them for a minimum of once a week for up to 6 months. An initial questionnaire will collect information on lifestyle factors and residence characteristics, such as type of cooker used in the home (eg, gas, electric or wood burning stove) and car ownership. During the study period, participants will complete daily diary cards of their symptoms, any changes to their treatment (eg, medications) and sleep disturbance. They will be asked to record their peak expiratory flow on the diary card using a peak flow meter. Spirometry readings will be collected at the initial appointment and subsequent follow-up visits if the participant consents. This will provide information on the severity of their condition and may control for possible random differences.

If at any stage the wearing compliance of the PAM is low, or the participant chooses to withdraw, a replacement will be recruited. Throughout the monitoring period, participants will receive phone calls from the research assistant to check how they are coping with the study. Six weeks into the monitoring period, participants will be invited to attend a clinic with the research assistant to discuss any issues with the PAMs or diary cards. At the end of the monitoring period (at 6 months or earlier if the participant wishes to withdraw), participants will be invited to a final appointment to return the PAMs and completed diary cards.

#### Use of anonymised EHR from CPRD

This is a consented study and, as such, participants will be asked to give their consent in the first appointment to the use of their anonymised data in the research analysis involved. CPRD will provide GOLD data sets to the chief investigator at Imperial College London which are then downloaded from the clinical IT system. Data will be stored against a ‘non-identifying’ identifier (first level anonymised) generated using a key held only by the general practice, so that they cannot be linked back to the data sets using Imperial College London's online access. A second key will be used to generate a further level of anonymisation at the CPRD data centre before any data are seen by researchers undertaking any aspect of the trial analysis. In order to comply with CPRD's approval from the Confidentiality Advisory Group of the Health Research Authority, there will be a reidentification risk management plan in place to prevent de-anonymising the CPRD. Since there is a way back via the two keys to check the validity of the data, this is technically a pseudoanonymisation. At the research end, however, patient data are effectively fully anonymised as there is no way that a researcher can obtain access to either of the two keys which are held securely in two different locations. The research assistant will only have access to the raw patient data (collected from the daily symptom diary cards, spirometry readings and questionnaire) and those performing the analysis will only have access to anonymised data. All data at whatever location will be stored in systems that fully meet all data storage requirements and have appropriate standard operating procedures.

### Statistical associations between personal exposure with COPD-related health outcomes

The monitoring phase of the project will create a unique high resolution multiparameter data set of individual exposure patterns over an extended period. These data will be mined to explore associations between participant's health (symptoms, lung function and exacerbations) and the environment through (1) direct measurements, (2) derived variables and (3) modelled outputs. Explanatory variables will include peak, mean and cumulative exposure, rate of change, activity level and pollutant dose/intake, lag effects, ambient pollution or temperature episode effects, pollutant source types (eg, traffic, regional, domestic) and indoor/outdoor ratios. The aim will be to identify and explain any observed associations, allowing the translation of results into healthcare relevant information and possible policy updates.

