### Development and long-term deployment of personal air pollution sensors

Personal air monitors (PAMs) have been designed, manufactured and tested specifically for the COPE study (figure 2). The PAMs can be either strapped around the waist with a belt or worn over the shoulder. A waterproof case will be provided to the participants to make it less conspicuous when worn outside the house. The PAMs will employ ubiquitous sensing of a large number of geotemporal environmental parameters that can be measured simultaneously (table 1). The measurements will be stored in the sensor and uploaded through General Packet Radio Service to a secure server through the charging base station. No interaction with the unit is required by the participant, other than to place it in its charger each night (the battery life of the sensor is 30 hours between charges). It will operate continuously and is almost silent.

**Table 1 BMJOPEN2016011330TB1:** Summary of monitored parameters of the PAMs

Parameter	Method	Monitoring interval
Spatial coordinates	GPS	20 s
Background noise	Microphone	100 Hz
Physical activity	Triaxial accelerometer	100 Hz
Temperature (°C)	Thermocouple	20 s
RH (%)	Electrical resistive sensor	20 s
PM_1_, PM_2.5_, PM_10_ (μg/m^3^)	OPC	20 s
CO, NO, NO_2_, O_3_ (ppb)	Electrochemical sensors	20 s

CO, carbon monoxide; GPS, Global Positioning System; NO, nitric oxide; NO_2_, nitrogen dioxide; OPC, optical particle counter; O_3_, ozone; PAM, personal air monitor; PM, particulate matter; ppb, parts-per-billion; RH, relative humidity.

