In total, 160 participants will be recruited from CPRD using an algorithm containing validated COPD diagnostic codes. Patients with data in CPRD who have a diagnosis of COPD based on a validated code list by Quint *et al*^21^ are not coded for mild COPD (ie, moderate or severe patients only), are not coded as a current smoker, are aged >35 years, and have had between one and two identified exacerbations in the preceding year will be included. After running the algorithm to identify suitable participants, general practices that have agreed to participate in research through CPRD will be sent a list of the potential participants. GPs will confirm to CPRD the suitable patients identified previously using the Vision Identification. CPRD will then send participant information packs to the general practices to disseminate to the potential recruits. The information pack will contain a cover letter from the general practitioner introducing the study, a participant information sheet with detailed information of what the project entails, and an expression of interest form that participants can complete and send to the research team in a prepaid envelope. Once received, the research team will then be able to contact the participant to enrol them in the study through a clinic appointment. Participants will also be recruited from respiratory clinics in secondary care as an additional recruitment option.

The sample size of 160 patients is based on the estimated number of exacerbations for the cohort. Since we will recruit with a bias towards patients with COPD with a history of COPD exacerbations, we have made the conservative estimate that we will capture at least 200 exacerbations with a cohort of 160 patients. We have calculated a minimum detectable relative risk (RR) to detect associations at p<0.05 with 80% power. With 200 exacerbations, this will permit detection of about RR=1.65 in the highest 20% of days compared with others (RR=2.00 in the highest 10%). Other more common outcomes and in particular peak flow will have power to detect smaller associations.^22^

Two secondary recruitment methods will be established to make up any shortfall in recruits through the CPRD: recruitment from respiratory clinics in local hospitals and presentations at British Lung Foundation ‘Breathe Easy’ respiratory disease support groups.

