### Development of a COPD prediction model

Associations between exacerbations with spatiotemporally resolved environmental exposure established in the Statistical associations between personal exposure with COPD-related health outcomes section will be combined with the time-activity exposure model (LHEM) to create a predictive model for COPD exacerbations across London. First, time-location-activity patterns of the COPD cohort will be compared with general population-level time-activity patterns derived from the Traffic Pollution and Health in London project.^24^ This will be used to test the applicability of general population behaviour patterns when assessing COPD associations in epidemiological studies.

The association between personal exposure to air pollution with COPD exacerbations estimated in the Statistical associations between personal exposure with COPD-related health outcomes section will form the basis of the COPD prediction model. This model will be used to create high resolution (20×20 m grid) daily COPD exacerbation risk maps for the years 2005–2011, based on modelled meteorological and pollutant conditions, coupled with typical patient with COPD time-activity patterns identified in the Activity algorithms section. The model will thus retrospectively predict days and locations more likely to trigger a worsening of symptoms and/or exacerbation in patients with COPD over this time period.

The performance of the predictive model will be evaluated using validated methods for patient identification^21^ from EHRs, CPRD, HES and ONS death data excluding data from the COPE cohort. Spatial and temporal patterns of recorded exacerbations will be compared with model risk estimates linked to the home address. If it is demonstrated that there are significant associations between model predictions and recorded exacerbations, the algorithms used will be generalised for use outside of London. These algorithms will provide an opportunity for the development of a national COPD forecasting service with proven performance in predicting increased risk of exacerbations.

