## Ethics and dissemination

CPRD has been granted Multiple Research Ethics Committee (MREC) approval to undertake observational studies and external data linkages with HES and ONS. Research and Development (R&D) approval has also been granted by the Royal Brompton and Harefield NHS Foundation Trust and Guy's and St Thomas' NHS Foundation Trust to carry out the study at the Clinical Research Facility in the Royal Brompton Hospital and the Lane Fox Respiratory Unit at St Thomas' Hospital (IRAS ref 166785). Ethical approval is being sought to collect blood and sputum samples from a subset of 20 participants for a pilot study.

Participants will be informed that the monitors use GPS technology and will provide spatial data at intervals during the day. Participants will be reassured that this information will only be accessed at the end of the study to analyse overall spatial and temporal relationships and not real-time movement. In addition, participants will be informed that the monitors will have a built-in microphone for the purpose of recording ambient (background) noise levels. It will not be used for the recording of speech.

The behavioural and environmental COPD associations identified during the study will be adapted for application on a national scale and disseminated to healthcare providers including the Department of Health, Clinical Commissioning Groups and GPs. Information will include evidence of environmental conditions and patient activities that are found to contribute to an increased risk of COPD symptoms and exacerbations. The predictive algorithms will be made available, allowing the development of a validated national COPD forecasting system. Such a system has the potential for further commercial exploitation and the research team will seek to collaborate with the UK Meteorological Office in order to improve the effectiveness of their Healthy Outlook service. This research would provide an opportunity to carry out a cost–benefit analysis of such a system, now essential for commissioning in the current health market.

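### An open exploratory search supplies the prediction model and national dissemination, while the stated power covers only one unadjusted contrast

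*Protocol article*

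**What the plan says.** **The search.** Under the heading on statistical associations between personal exposure and COPD-related outcomes: "These data will be mined to explore associations between participant's health (symptoms, lung function and exacerbations) and the environment". The candidate list is open: "Explanatory variables will include peak, mean and cumulative exposure, rate of change, activity level and pollutant dose/intake, lag effects", followed by ambient episodes, source types and indoor/outdoor ratios. The stated aim is to explain whatever associations are observed. Table 1 gives nine environmental exposures: three particle fractions, four gases, temperature and relative humidity.

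**The power statement.** Under recruitment of panel participants: "We have calculated a minimum detectable relative risk (RR) to detect associations at p<0.05 with 80% power". It assumes that "we will capture at least 200 exacerbations with a cohort of 160 patients", and gives a detectable RR of about 1.65 for the highest 20% of days against the rest, and 2.00 for the highest 10%. It does not say which exposure, metric or lag defines a high day.

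**The uses.** In the section on the prediction model, the association between personal air pollution exposure and exacerbations "will form the basis of the COPD prediction model". The model's performance is then evaluated in health records that exclude the COPE cohort. The algorithms go beyond London only if predictions and recorded exacerbations are significantly associated. Under ethics and dissemination: "The behavioural and environmental COPD associations identified during the study will be adapted for application on a national scale and disseminated to healthcare providers". That sentence carries no such condition.

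**The concern.** The analysis is described as exploratory, but its output is used as if it were established. The one stated error rate and power figure belong to a single contrast, whereas the association that reaches the model or the healthcare providers will come from a search over many. Two things follow. A nominally significant association can arise by chance much more often than 5% of the time. And where the estimate is imprecise, those that look significant are on average too large. The article's introduction describes earlier pollutant effects on COPD admissions and mortality as small, which is the setting where such exaggeration is worst. An inflated coefficient would pass into the daily 20×20 m risk maps, and the association itself into information for the Department of Health, commissioning groups and GPs.

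**Working it through.** **1. Reproduce the plan's own figure.** Inputs from the recruitment section: 200 exacerbations, 20% of days exposed, p<0.05 (two-sided assumed, as the article does not say), 80% power.

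- With 40 events expected on high days and 160 on the others under no effect, SE(log RR) = √(1/40 + 1/160) = 0.177.
- Detectable RR = exp((1.96 + 0.84) × 0.177) = 1.64, against a stated 1.65.
- Events needed for RR 1.65 = (1.96 + 0.84)² / (0.2 × 0.8 × (ln 1.65)²) ≈ 196, against 200. Power at 200 events is 80.9%.
- For the highest 10% of days: SE = 1/√(200 × 0.1 × 0.9) = 0.236 and detectable RR = 1.94, against a stated 2.00, which is slightly conservative.
- A one-sided test would need only 155 events at RR 1.65, so it does not fit.

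The figure is therefore right for one unadjusted two-sided contrast.

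**2. Size of the search (assumption).** The article gives no number of tests. These grids are built from its own lists, with one lag:

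- 9 exposures × 4 metrics (peak, mean, cumulative, rate of change) × 3 outcome domains = 108.
- Exacerbations only: 9 × 4 = 36, or 7 pollutants × 4 = 28.

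Dose, episodes, sources, ratios and further lags are left out.

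**3. Chance of at least one p<0.05 with no true effect.** If tests were independent this is 1 − 0.95^k. Pollutants and metrics are correlated, so correlated null z-scores were also simulated, counting sets with any |z| > 1.96. Moderate means correlations of 0.5 between exposures, 0.7 between metrics and 0.3 between outcomes. Strong means 0.7, 0.9 and 0.5.

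| Grid | Tests | Independent | Moderate | Strong |
|---|---|---|---|---|
| 9 exposures × 4 metrics × 3 outcomes | 108 | 99.6% | 91% | 67% |
| 9 × 4, exacerbations only | 36 | 84% | 57% | 34% |
| 7 × 4, exacerbations only | 28 | 76% | 50% | 30% |
| 9 × 1, exacerbations only | 9 | 37% | 27% | 20% |

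Adding three lags (correlation 0.7) to the 36-test moderate case gives 84%.

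**4. Exaggeration of a selected estimate.** For the top-20%-of-days contrast, the smallest significant RR above 1 is exp(1.96 × 0.177) = 1.41. Suppose the true RR is 1.10 (assumed, to represent a small effect). Then power is P(Z > (ln 1.41 − ln 1.10)/0.177) = P(Z > 1.42) ≈ 8%, and estimates that are significant and positive average about 1.53.

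**5. What adjustment would do to the stated power.** Bonferroni detectable RR = exp((z at 1 − 0.025/m + 0.84) × 0.177): 1.90 for m = 9, 2.01 for m = 27 and 2.15 for m = 108. Power for RR 1.65 falls to 52% at m = 9 and 39% at m = 27.

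**6. Effect of the out-of-cohort test.** If a chance finding must also pass one independent test at 0.05, it survives both steps with probability (1 − 0.95^27) × 0.05 = 0.75 × 0.05 ≈ 4% for 27 independent tests, and never more than 5%.

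**The case against.** Several points on the other side stand.

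- **No selection rule is stated.** The p<0.05 appears only as an input to the power calculation. Nothing says that a p-value decides what enters the model or is disseminated. The probabilities above describe nominal significance, not a written decision rule.
- **The work is called exploratory**, and a multiplicity rule may sit in an analysis plan or full protocol that is not shown. Its absence from an article is not itself an error.
- **The outcome is already named.** Both the power statement and the prediction model rest on exacerbations. What remains open is the exposure, metric and lag. The 108-test grid is therefore wider than the search that feeds the model.
- **External evaluation exists.** The model is tested in records outside the cohort, and extension beyond London depends on the result. Step 6 shows that this is a strong filter against pure chance.
- **The 1.41 floor is specific** to the binary top-20% contrast. A per-unit hazard ratio on a continuous exposure has no such floor.

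A reader might infer that a false association reaching the model is more likely than not. The documents do not support that: the exacerbation-only grids give 30-57%, depending on assumed correlations. A reader might also infer that national forecasting would rest on unchecked chance findings. The condition in the prediction-model section rules that out for the algorithms.

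The external test does not settle two matters. It does not govern which coefficient enters the London model or correct its size, since an inflated coefficient can still rank days correctly and pass a test of association. And it concerns model predictions, whereas the dissemination sentence concerns the associations themselves, including behavioural ones.

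**Conclusion.** The concern holds in a limited form. The article fixes a mismatch: an open search, two uses that treat its product as established, and a power figure valid for one unadjusted contrast. With no true effect, the chance of at least one nominally significant result is about 67-91% over the assumed 108-test grid and about 30-57% over exacerbation-only grids of 28-36 tests. These figures rest on assumed test counts and correlations, because the article states neither. The exaggeration figure (8% power, mean significant positive RR about 1.53) rests on an assumed true RR of 1.10 and applies only to the top-20%-of-days contrast. Use of the algorithms outside London is already protected. The choice and size of the London model's coefficients, and the dissemination of associations, are not. This should be changed, but it does not invalidate the design.

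**What to change.** Before exposure data are linked to outcomes:

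1. Name the exposure, metric and lag for the exacerbation association to which the p<0.05, 80% power and RR=1.65 statement applies, and say that it applies to that association alone.
2. Label all other exposure, metric, lag and outcome combinations exploratory, and report them with false-discovery-rate control.
3. Estimate the prediction model's coefficients with penalisation and cross-validation.
4. In the dissemination section, present as established only the pre-named association, or those supported by the planned out-of-cohort evaluation. Disseminate the rest as exploratory.

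The fourth step should not require every association to be reproduced in CPRD or HES data. Those records hold no personal exposure or activity measurements, so behavioural associations could not be tested there.

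The cost is wording and some extra analysis work, with no new patients or data. The downside is that exploratory associations carry less weight.

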### Statistical analysis

Survival analyses for repeated measurements will be performed on the basis of the Cox proportional hazards model. Interval censoring for handing ties over appropriate event time intervals will be applied specifying each participant to a stratum. Essentially, conditional regression will be used to estimate the HR of subjective health symptoms and exacerbations in relation to seasonal variations of personal exposure (prognostic factor). The conditional regression models will be developed by the PHREG procedure in SAS V.9.3 (North Carolina, USA) with robust sandwich covariance for aggregated data. Ties will be handled with the DISCRETE method. Medication use will be inserted as a control factor in the models.

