## Introduction

Chronic obstructive pulmonary disease (COPD) is a chronic progressive disease associated with the abnormal inflammatory response of the lungs to noxious particles or gases^1^ and is characterised by increased resistance to airflow in small conducting airways, changes in lung compliance and the premature collapse of airways during expiration.^2^ The inflammatory responses can lead to increased sputum production, breathlessness and reduced lung function, often resulting in reduced exercise tolerance and decreased quality of life.^3^
^4^ COPD has a large burden on healthcare resources with an estimated annual cost to the National Health Service (NHS) currently of over £800 million.^5^ At present, it is the fourth leading cause of death worldwide, and it is predicted that total deaths from COPD may increase by more than 30% in the next 10 years unless urgent action is taken to reduce the underlying risk factors.^6^

Smoking is the most important risk factor for COPD; however, an estimated 25–45% of patients have never smoked. Other risk factors include a history of pulmonary tuberculosis, chronic asthma, childhood respiratory tract infections, occupational exposure to dusts and gases, air pollution and low socioeconomic status.^7^ The prevalence of COPD is increased in individuals living close to traffic,^8^ and patients with COPD have substantial mortality risks associated with particles^9^ and temperature changes.^10–12^ Exacerbations of COPD are acute episodes of deterioration associated with increased mortality and decreased quality of life, and are the second most common cause of adult emergency medical hospital admission in the UK.^8^ Infections, both bacterial and viral, are known to play a major role in exacerbations.^4^

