### Use of EHR to analyse exacerbations

CPRD GOLD data sets will be used to identify general practitioner-treated COPD exacerbations. Information from Hospital Episode Statistics (HES) and the Office of National Statistics (ONS) will also be gathered from CPRD including: accident and emergency admissions, hospital admissions and mortality. Mortality data from ONS will be used as a severity index for exacerbation. Figure 3 shows the covariates and comorbidities to be used in the statistical analysis of COPD exacerbations. Spatial and temporal patterns of recorded exacerbations extracted from historical CPRD, HES and ONS records will be compared with model risk estimates, with the aim of deriving predictive algorithms for future hospitalisations.

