## Discussion

Several studies have attempted to identify relationships between environmental factors and COPD exacerbations.^25^
^26^ However, limitations of the methodological design of previous studies have made it difficult to identify clear links between exposure and health outcomes.

The strength of this study lies in the fact that we will have the ability to assess these associations in far more detail, initially at the individual patient level and potentially at a national level.

For the first time, this study will provide a multidisciplinary methodological framework that will bring together recent advancements in low-cost wearable sensors, computational techniques for the estimation of activity-weighted personal exposure and advanced spatial mapping in a well-characterised population study. The integrated database of environmental stressors and activity patterns at the individual level will form the basis for the validation of the LHEM. The LHEM can further incorporate spatial and temporal patterns of recorded exacerbations extracted from historical CPRD, HES and ONS records to form a COPD prediction model for future hospitalisations.

Limitations include the fact that participants will be asked to participate in the study for up to 6 months in order to try and capture seasonal changes in exacerbations and some may be dissuaded by this. Despite the process of identifying and recruiting patients via CPRD, there may be insufficient numbers of patients who are interested in participating to power the study. Owing to these recruitment concerns, we are not planning to request blood and sputum samples from all participants, and this means that we will not have any biological data from some participants to assess physiological and inflammatory changes during their exacerbations. However, funding has been obtained for a substudy within COPE to collect blood and sputum samples in a subset of 20 participants at baseline, exacerbation and 4 weeks post exacerbation.

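### Participant strata with a seasonal exposure contrast leave infection and other seasonal causes confounded with pollution, and do not match the day-level effect that the study powers and maps

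*Protocol article*

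**What the plan says.** All references are to the Protocol article.

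- **Stratum.** Statistical analysis fits a Cox-type conditional model "specifying each participant to a stratum". No month, season or other time block is part of the stratum.
- **Contrast.** The same section says that "conditional regression will be used to estimate the HR of subjective health symptoms and exacerbations in relation to seasonal variations of personal exposure".
- **Control.** It adds: "Medication use will be inserted as a control factor in the models". No other adjustment term is named there.
- **Time intervals.** "Interval censoring for handing ties over appropriate event time intervals will be applied". The intervals are not defined, and their stated use is for ties.
- **Other covariates.** Under Use of EHR to analyse exacerbations: "Figure 3 shows the covariates and comorbidities to be used in the statistical analysis of COPD exacerbations". The figure is not shown. Its caption describes covariates and comorbidities taken from health records.
- **Temperature.** The section on associations between personal exposure and health outcomes lists temperature episodes among the explanatory variables, not as an adjustment in the pollutant models.
- **Seasonal causes.** Introduction: "Infections, both bacterial and viral, are known to play a major role in exacerbations". Discussion: participants are followed "for up to 6 months in order to try and capture seasonal changes in exacerbations".
- **Use of the estimate.** Recruitment of panel participants powers high-exposure days against other days. Development of a COPD prediction model takes the estimated association as the basis for daily risk maps.

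**The concern.** A model stratified by participant compares a person's event days with the same person's other days, here over as much as half a year. Fixed differences between people cancel. Whatever changes over those months does not. If the exposure contrast is itself seasonal, every other seasonal cause of exacerbation moves with it. The article supplies one such cause (infection) and expects exacerbations to be seasonal.

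Two things are at stake. First, the hazard ratio may carry a seasonal component that is not due to the pollutant, in either direction, and the London prediction model would inherit it. Second, a seasonal contrast does not answer the question that the power statement and the daily maps pose, which is what happens on a high-exposure day compared with another day near it.

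**Working it through.** **1. The plan's own figure.** Inputs from Recruitment of panel participants: 200 exacerbations, p<0.05 (taken as two-sided), 80% power, share of high-exposure days p = 0.20 or 0.10.

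Minimum RR = exp[(1.960 + 0.842)/√(200·p·(1−p))]

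- p = 0.20: exp(2.802/√32) = 1.641. The article says about 1.65, so this reproduces. Power at 1.65 is 80.9%.
- p = 0.10: exp(2.802/√18) = 1.935. The article says 2.00, which is on the cautious side.

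The formula is for a day-level contrast with no adjustment for season.

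**2. Direction of the bias, in closed form.** Assume no pollutant effect and a six-month window, half of it at baseline risk and half at W times that risk. Let a fraction f of the top-20% exposure days fall in the high-risk half.

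- Mean risk on exposed days: fW + (1−f).
- Share of the other days in the high-risk half: g = (0.5 − 0.2f)/0.8. Their mean risk is gW + (1−g).

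| W | f = 0.3 | f = 0.5 | f = 0.7 |
|---|---|---|---|
| 1.5 | 1.150/1.275 = 0.90 | 1.00 | 1.350/1.225 = 1.10 |
| 2 | 1.30/1.55 = 0.84 | 1.00 | 1.70/1.45 = 1.17 |
| 3 | 1.60/2.10 = 0.76 | 1.00 | 2.40/1.90 = 1.26 |

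The sign depends on whether high exposure falls in the high-risk or the low-risk season.

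**3. Simulation with true RR = 1.** Assumptions, none of them in the article: start dates spread over the year, 26 weeks per person, sinusoidal season, winter:summer risk ratio W, season explaining a share R² of exposure variance, and exposure peaking together with exacerbations. RR with participant strata:

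| R² | W = 1.5 | W = 2 | W = 3 |
|---|---|---|---|
| 0.2 | 1.06 | 1.14 | 1.19 |
| 0.4 | 1.11 | 1.17 | 1.27 |
| 0.7 | 1.14 | 1.23 | 1.39 |

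Repeated runs differ by a few hundredths, so the range is best read as about 1.05 to 1.4. With exposure peaking in the opposite season the range is about 0.66 to 0.94. With strata of participant by about 28 days, RR is about 1.0 in both directions.

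A separate simulation at trial size (160 people, 182 days, about 200 events, 200 replicates) used milder exposure seasonality: sine amplitude 0.5 or 1.0 against day-to-day SD 1, so R² = 0.125/1.125 = 11% or 0.5/1.5 = 33%. Participant strata gave RR 1.07-1.23 and type I error 6-22% for W from 1.5 to 3. The 28-day strata gave RR 0.99-1.02 and 2.5-7%.

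**4. Type I error with 200 events.** SE = 1/√(200·0.2·0.8) = 0.177.

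- RR 1.06: ln(1.06)/0.177 = 0.33, and Φ(−1.63) + Φ(−2.29) = about 6%.
- RR 1.39: ln(1.39)/0.177 = 1.86, and Φ(−0.10) = about 46%. This is the extreme corner (W = 3, R² = 0.7). Repeated runs put it at 45-50%.

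**5. Size against the planned effect.** ln(1.05)/ln(1.65) = 0.049/0.501 = 10%, and ln(1.4)/ln(1.65) = 0.336/0.501 = 67%. In the masking direction, if the bias multiplies the true effect, an RR of 1.65 would appear as about 1.65 × 0.66 = 1.09 to 1.65 × 0.94 = 1.55.

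**6. Cost of controlling season.** If season absorbs a share R² of the variance of the exposure as analysed, replace 200 by 200(1−R²) in step 1.

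| R² (assumed) | Min RR, top 20% | Min RR, top 10% | Power at 1.65 | Power at 2.00 |
|---|---|---|---|---|
| 0 | 1.641 | 1.935 | 81% | 84% |
| 0.2 | 1.740 | 2.092 | 72% | 75% |
| 0.5 | 2.015 | 2.544 | 52% | 55% |

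In the simulations a top-20%-of-days indicator lost less: SE rose by 4-24%, that is a minimum RR of exp(0.495 × 1.04) = 1.67 to exp(0.495 × 1.24) = 1.85. Smooth or cumulative exposures lose more.

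**The case against.** The strongest reply is that this is a condensed article. Splines of time, temperature terms and lag structure are usually left to the full plan, and their absence is no fault. That is fair, and absence is not the point here. The section states the stratum and the contrast outright, and those two choices together produce the confounding.

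Other replies, and what remains of each:

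- *Figure 3 may supply control.* It is not shown and could include an infection code. But it is described as record-based covariates and comorbidities. A calendar-time term there is unlikely, and comorbidities that stay constant over six months drop out of a participant-stratified likelihood.
- *The undefined event time intervals could be short blocks.* If so, they would remove the seasonal contrast that the next sentence sets out to estimate. Either way the text needs correction.
- *The study means day-level effects.* The power statement, the lag and rate-of-change variables and the daily maps suggest this. It supports rewording the contrast.
- *The amplitudes are assumed.* This stands. The article gives no seasonal pattern for exposure to any pollutant, or for exacerbations.

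A reader might go further and infer that a harmless pollutant is bound to show a positive association. The documents do not support that: the sign depends on when exposure peaks. Nor does it follow that half a year per person cannot separate exposure from season, because short strata do so in the simulations. A weekday bias might also be suspected, but nothing in the article says that events or exposure follow the working week.

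**Conclusion.** The point holds as a risk of bias in either direction, built into the stratum and contrast as written. Infection and other seasonal causes can be credited to pollution, or can hide a true effect. In addition, the seasonal contrast is not the day-level effect that the study powers and maps.

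The size rests wholly on the assumed seasonal amplitudes, and the upper end of the type I error belongs to the extreme case only. What does not depend on those amplitudes is the mechanism: participant strata cannot remove a cause that varies within the person over the follow-up. The published figure of about 1.65 is arithmetically sound for the contrast it describes, but it allows nothing for seasonal control.

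**What to change.** 1. Restate the effect to be estimated as that of short-term, within-month exposure.
2. Define strata as participant by calendar month. Alternatively, keep participant strata and add a smooth function of calendar time.
3. State that temperature is adjusted for in the pollutant models.
4. Define the event time intervals and say whether they enter the stratum.
5. Report the seasonal contrast separately, as descriptive only.
6. Restate the minimum detectable RR after seasonal control, with the assumed share of exposure variance given: for the top 20% of days, about 1.74 at 20% and about 2.015 at 50%.

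The change affects the analysis only and needs no new data. Its price is precision: standard errors about 4-24% wider for a top-20%-of-days indicator, and more for smooth or cumulative exposures. That loss is a reason to restate power, not to keep a contrast that season can explain.
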